## Abstract

**Background:**

Long term survivors of childhood cancer have a high prevalence of chronic pain. Novel, multidisciplinary approaches to manage pain, are needed to allow for a reduction in the use of opioids for pain management. Physical activity is highly effective in managing chronic pain in children and adolescents, however, evidence about the combination of physical activity intervention and pain medications in chronic pain management in childhood cancer survivors is lacking. The aim of this study is to investigate the feasibility, acceptability and preliminary effects of a behavioral physical activity intervention integrated into standard post cancer directed treatment care to mitigate chronic pain in this unique population.

**Methods:**

This is a single site pilot randomized controlled trial of a 16-week physical activity intervention coupled with standard care. The primary aim is to assess the feasibility and acceptability of the physical activity intervention in childhood cancer survivors with chronic pain. Secondary aims include evaluating the differences in functional and psychosocial outcomes along with self-reported pain scores and cumulative dose of pain medications between the exercise group and standard cancer care group. The physical activity intervention is a home-based program structured to increase patients' physical activity behavior and to favor low intensity bodily movement using aerobic exercise and resistance training.

**Conclusions:**

This study will demonstrate that behavioral supportive measures like physical activity may be a novel means to improve cancer related chronic pain in young survivors of childhood cancer and decrease medication usage for pain along with improvement in functional and psychosocial outcomes.

## Introduction

1

Chronic pain is defined as persistent or recurrent pain lasting longer than 3 months [1] and affects one in four Americans [2]. Its annual cost ($635 billion) is greater than the annual costs of heart disease ($309 billion) and cancer ($243 billion) combined [3]. In the general pediatric population, chronic pain affects up to 35% of children and adolescents worldwide [4], leading to physical and mental health difficulties [5,6].

In long-term survivors of childhood cancer, the prevalence of chronic pain ranges from 11.0% to 43.9% across studies [7]. Moreover, 1 in 2 children and adolescents diagnosed with cancer who experience chronic pain will progress to adulthood with chronic pain, even 25.5 years after being diagnosed with cancer [8]. Evidence shows that childhood cancer survivors (CCS) are more likely to report pain compared to their healthy peers [9]. Moreover, the frequency of chronic pain increases with age, with a higher prevalence during adolescence as compared to earlier in childhood [10,11] with girls reporting chronic pain more frequently than boys [12,13]. There are several reasons for chronic pain in CCS, such as the long-term adverse effects of cancer and treatments and the invasive procedures they received during their disease trajectory [7,14,15].

Treating chronic pain early on is important because if pain continues into adulthood [8,16], it is often more difficult to treat, as observed in patients without cancer [[17], [18], [19]]. Chronic pain in children and adolescents has been associated with reduced physical function and physical activity (PA) levels, with resultant effects on mental health and psychosocial wellbeing (quality of life, anxiety, depression, fatigue) [5,6,13,20]. While non-opioid medications are used to treat mild to moderate chronic pain, opioid medications are often given to treat moderate to severe chronic pain [21] which can be highly addictive, especially among youth in the United States [22,23]. The proportion of patients diagnosed with cancer who receive opioid pain medication ranges from 6% to 46% across studies.

Multidisciplinary approaches to manage chronic pain are needed to improve the quality of life of the CCS and to reduce the use of opioids which would also have the benefits of improving CCS' physical and psychosocial health [24]. There is growing evidence for the positive effects of non-pharmacological interventions such as PA training on organ function, fatigue and physical well-being in children during and after treatment for cancer [25]. PA has been shown to be a promising intervention to improve fitness, biomarkers of cardiometabolic health, inflammation and adipokines among adult cancer patients and children, adolescent and young adult cancer survivors [26,27]. Changing health behaviors through exercise training could help children and adolescent cancer survivors increase their time out of bed, change their sedentary lifestyles and get them to be more physically active, avoid physical deconditioning from inactivity and lead to improvements in mental and physical health.

We recently hypothesized that integration of PA into the management of patients' chronic pain could be an effective strategy to effectively mitigate pain while simultaneously reducing the use of pain medications [24]. We believe that PA could reframe the pain sensation and improve body sensations along with increasing pain tolerance. A systematic review and meta-analysis reported that conditioned pain modulation is impaired in populations with chronic pain and pain pressure thresholds are reduced [28,29]. It has been postulated that PA can improve pain inhibition through changes in the central nervous system resulting in a decrease in pain sensitivity [30] and reports suggesting the association of exercise training with equal or reduced pain sensitivity have been published [31,32]. Observations have shown that exercise training stimulates regions of the brain to improve the functional capacity of the pain modulatory mechanisms [33].

Given the evidence that exercise training has the potential to mitigate chronic pain through reframing pain sensations and sensitivity, we planned a randomized controlled two arm exercise intervention trial to demonstrate that integration of PA into standard cancer care will improve patient reported chronic pain, decrease the need for medications to manage chronic pain and improve functional and psychosocial outcomes in young survivors of childhood cancer.

## Objectives

2

The primary objective of this single-center, pilot randomized controlled trial is to determine the acceptability and feasibility of a 16-week behavioral PA intervention coupled with standard post-cancer directed treatment care in children and adolescent survivors of childhood cancer. The secondary objectives are to compare changes in chronic pain levels, cumulative dose of pain medications, physical function, and patient-reported outcomes within-group (CCS receiving behavioral PA intervention coupled with standard post-cancer directed treatment care and CCS receiving standard post-cancer directed treatment care alone) and between the two groups.

## Material and Methods

3

This manuscript adheres to the Standard Protocol Items: Recommendations for Interventional Trials (SPIRIT) Checklist [34]. The trial was registered on ClinicalTrial.gov (NCT05562193).

### Study design

3.1

This is a single-site pilot randomized controlled trial where participants will be randomized in a 1:1 ratio to the 16-week behavioral PA intervention coupled with standard post-cancer directed treatment care, or to the standard post-cancer directed treatment care.

### Ethical approval

3.2

This study will be conducted in accordance with the Declaration of Helsinki. The study protocol was approved by the Penn State University Institutional Review Board (#00020762).

### Participants screening

3.3

Potential participants will be identified through the Division of Pediatric Hematology and Oncology's Comprehensive Operational Database within the Penn State Health Children's Hospital at the Milton S. Hershey Medical Center, and through Penn State Cancer Institute located in Hershey, Pennsylvania in the United-States. The research coordinator will contact the patient's medical oncologist for medical clearance and approval to approach the patient's family (parents or legal guardians) to present the study. If research staff are not able to contact the patient's medical oncologist to obtain their approval to approach their patients, potential participants will not be approached or enrolled.

### Participants eligibility

3.4

A total of 20 participants will be enrolled following these inclusion and exclusion criteria.

#### Inclusion criteria

3.4.1

1)Male and female CCS diagnosed with any type of cancer;2)Completed all standard/planned cancer treatment and are stable at the time of enrollment;3)< 1-year post cancer therapy;4)Have chronic pain (pain will be self-reported by the participant, will have to be ≥ 1 on a scale of 10 and lasting for 3 months or longer);5)Between 10 and 17 years old at the time of enrollment;6)Who are and who are not non-ambulatory/wheelchair bound;7)Parent/legal guardian must be able to speak, read and understand the English language;8)Parent or legal guardian must be able to provide and understand informed consent;9)Participants must be able to provide and understand assent;10)Participants must be able to attend visits at Penn State Health Children's Hospital;11)Participant and parent/legal guardian must have access to a computer, smartphone or tablet.

#### Exclusion criteria

3.4.2

1)CCS who have not completed all standard/planned cancer treatment and/or not in complete remission at the time of enrollment;2)> 1-year post cancer therapy;3)< 10 years old and >17 years old at the time of enrollment;4)CCS who have evidence in their medical record of an absolute contraindication to complete any of the physical assessments. This exclusion criterion is at the oncologist's discretion and can be applicable any time during the study. Research staff will be informed of the absolute contraindication when they contact the medical oncologists via secure email or secure messaging through the electronic medical record for approval to approach their patients for the study and for medical clearance.5)CCS who have history of refractory or recurrent cancer;6)Participants or their parent/legal guardian who are unable to speak, read, and understand the English language;7)CCS who are unable to access and complete online questionnaires.

### Enrollment and consent/assent procedures

3.5

The informed consent document will be reviewed in-person with the potential participants and their parents or legal guardians. All the potential questions related to the study will be answered. All eligible and interested participants will be consented for study participation by an approved study team member. To ensure that children and adolescents (between 10 and 17 years old at the time of enrollment) give assent without parental influence, they will be asked to give a fair explanation of the study without the help of their parents. They will be asked personally if they agree to participate before giving their assent. Written informed consent will be obtained from parents or legal guardians and assent will be obtained from the participants prior to the initiation of any study-related activities.

Participants and their parents or legal guardians will be informed that their participation in the research is voluntary, that their specific information will be de-identified, and that their decision to participate in this research study will not affect their care. Specific language in the consent document will allow to clarify that the relationship with their medical oncologist will not be altered if they choose not to consent to the research or choose to withdraw later. If enrolled participants request withdrawal from the study, we will ask for their withdrawal reasons and no further contact will be made. The participants and their parents or legal guardians will be informed that their data that was already collected can be retained and/or not included in the analysis according to their decision. The request for previously collected data to be removed from the analysis must be provided to the study team in writing.

### Randomization process

3.6

A computerized random number generator will be performed to randomly assign each participant to the behavioral PA intervention coupled with standard post-cancer directed treatment care group (n = 10) or the standard post-cancer directed treatment care group (n = 10) in the order they are enrolled (randomly, without the ability to predict the next assignment). A staff member not associated with the enrollment of the participants will create an envelope for each of the participants to be enrolled (n = 20). The envelopes will be sealed. Thus, staff members involved in the recruitment will not have any influence on the allocation of the patients.

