### Statistical analysis

3.18

Sample size calculations were not required for this single-site, pilot randomized controlled trial. The sample size of 20 is justified due to the limited availability of participants with the specific eligibility criteria being investigated.

Acceptability will be assessed and expressed as a percentage as follows: (number of patients enrolled × 100/number of patients approached).

Feasibility will be assessed by the number of participants randomized to the behavioral PA intervention coupled with standard post-cancer directed treatment care who complete more than 50% of the intervention calculated and expressed as a percentage, as follows: (number of interventions completed × 100/number of interventions planned). To note, the planned interventions are the support calls and text messages, as follows: weekly support calls (weeks 1–4), biweekly support calls (weeks 6 and 8) and texts (weeks 5 and 7), monthly support calls (weeks 12 and 16) and texts (weeks 9, 10, 11, 13, 14, 15).

The effects of the behavioral PA activity intervention coupled with standard post-cancer directed treatment care on secondary outcomes (total self-reported pain score, cumulative dose of pain medications, functional and psychosocial outcomes) will be explored using Repeated Measures Analysis of Variance (RM-ANOVA). RM-ANOVA [49] will be used to analyze both within-group and between-group differences in intervention effects. Cohen's *d* effect sizes [50] will be reported to quantify the magnitude of differences over time and to interpret the practical significance of the findings.

Drop-out and missing data will be accounted for and reported. If the reason is an adverse event during the intervention, it will be reported as well. In case of dropouts or missing data, an intention-to-treat analysis will be performed.

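### One unstratified list of 10 + 10 very mixed children, with no baseline covariate named, leaves the exploratory medication and pain comparisons open to chance imbalance

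*Protocol article*

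**What the plan says.** Section 3.4 fixes the size: "A total of 20 participants will be enrolled following these inclusion and exclusion criteria". Section 3.1 states that "participants will be randomized in a 1:1 ratio", and section 3.6 makes this 10 and 10. Section 3.6 describes the allocation: "A computerized random number generator will be performed to randomly assign each participant", "in the order they are enrolled (randomly, without the ability to predict the next assignment"), with 20 sealed envelopes made by someone outside enrolment. It mentions no stratum and no minimisation factor.

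The inclusion criteria in 3.4.1 are broad: "Male and female CCS diagnosed with any type of cancer", ages 10 to 17, ambulatory or not, and self-reported pain that "will have to be ≥ 1 on a scale of 10 and lasting for 3 months or longer". Taking an opioid is neither required nor excluded.

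The only figure for opioid use is in the Introduction: "The proportion of patients diagnosed with cancer who receive opioid pain medication ranges from 6% to 46% across studies".

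Section 3.18 explores the secondary outcomes ("total self-reported pain score, cumulative dose of pain medications, functional and psychosocial outcomes") by repeated-measures ANOVA within and between groups, with Cohen's d. It names no baseline covariate. Sections 3.13 and 3.14 collect prescribed and over-the-counter pain medicines and calculate a morphine-equivalent dose per patient.

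**The concern.** Two facts known at baseline bear strongly on these secondary outcomes. A child not taking an opioid has no opioid dose to reduce, and a child who enters with little pain has little room to improve. With 10 children per arm, chance alone can place most of the opioid users, or most of the children with high pain, in one arm. The between-arm contrast in dose, and to some degree in pain, would then partly reflect that split.

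The practical risk is to what follows the trial. The Conclusion says that the pilot should lead to a fully powered efficacy trial, and section 3.18 reports Cohen's d. An effect size shaped by an uneven split would be a poor guide to that next trial.

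**Working it through.** **Inputs.** N = 20 (3.4); 10 per arm (3.6); opioid prevalence q between 6% and 46% (Introduction). The range describes cancer patients in general, so applying it to children less than 1 year off therapy with chronic pain is an assumption. The value 20% is an illustrative point inside it. Section 3.18 gives no power calculation, so there is no planned figure to reproduce beyond 10 + 10 = 20.

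**Expected number of users.** 20 × 0.06 = 1.2 and 20 × 0.46 = 9.2, so about 1 to 9.

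**All k users in one arm, fixed 10 + 10 list.** P = 2 × C(10,k) / C(20,k) for k ≥ 2.
- k = 2: 2 × 45/190 = 0.474
- k = 3: 2 × 120/1140 = 0.211
- k = 4: 2 × 210/4845 = 0.087
- k = 5: 0.033; k = 6: 0.011; k = 8: 0.001; k = 9: below 0.001

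Complete separation is thus a realistic risk only with few users. With more users the likelier problem is a partial imbalance: with 4 users, 3:1 or worse has probability 0.582; with 8 users, 6:2 or worse 0.170; with 9 users, 6:3 or worse 0.370.

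**Averaged over k ~ Binomial(20, q).**

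| q | At least one user, and one arm has none | Of which exactly one user | Two or more users, all in one arm |
|---|---|---|---|
| 6% | 0.497 | 20 × 0.06 × 0.94^19 = 0.370 | 0.127 |
| 20% | 0.192 | 20 × 0.20 × 0.80^19 = 0.058 | 0.134 |
| 46% | 0.004 | below 0.001 | 0.004 |

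A lone user sits in one arm under any scheme. Only the last column is a risk that the design could reduce.

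**Entry pain.** For a roughly normal baseline variable, the standardised difference in means has SD √(2/10) = 0.447. P(|difference| ≥ 0.5 SD) = 2 × [1 − Φ(0.5/0.447)] = 0.26.

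**Consequence for the dose contrast.** This was simulated under no treatment effect. Users' doses were lognormal, non-users' doses zero, and users tapered by the same random fraction in both arms. The change in dose was compared by t-test. Over all allocations the false-positive rate was 3% to 4%. Given the split, it was about 34% at 4:0, 20% at 5:1 and 85% at 6:0 (a split with probability 0.011), and about 0 at an even split. The dose distribution is assumed, so these figures show the mechanism and do not forecast this trial.

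**Effect of stratifying by baseline opioid use.** With blocks of 2 inside the user stratum, the arms differ by at most 1 user; with blocks of 4, by at most 2. A block of 4 of which only two places are filled can still put both users in one arm, with probability 2 × (2/4) × (1/3) = 1/3. Three or more users cannot all fall in one arm with either block size.

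**The case against.** The strongest reply is that nothing here is invalid. Simple randomisation protects the type I error over all allocations, which the simulation confirms. The affected outcomes are secondary and exploratory, and the primary aims of acceptability and feasibility do not depend on them. Power at 10 per arm stays low whatever the allocation: about 20% for d = 0.5 and 43% for d = 0.8. All of this stands.

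Three stronger readings are tempting, and the documents do not support them.

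- A reader might infer a 50% chance of an uninformative opioid comparison at 6% prevalence. Of those 50 points, 37 come from a single user, whom no scheme can balance.
- A reader might infer that the whole medication outcome rests on 1 to 9 children. The outcome covers all pain medications, including over-the-counter products, so its users may exceed 9. A child not on an opioid at baseline may also start one.
- A reader might infer that a baseline gap would decide the pain result. Pain is measured at baseline, week 8 and week 16 and analysed over time, so the gap does not pass straight into the contrast. The entry rating out of 10 is also not the outcome instrument, which is the PedsQL pain questionnaire. The 26% measures baseline imbalance, not a wrong conclusion. Even so, analysing change does not remove floor effects or regression to the mean.

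Two further points carry weight. The text is an article, and a full protocol might name a balancing factor, although section 3.6 reads as a complete mechanism and hints at none. Balancing also has a price: in 20 children at one unblinded site, minimisation or small blocks make assignments somewhat easier to guess.

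**Conclusion.** The point holds as a vulnerability of exploratory comparisons, not as a flaw in the randomisation. One list of 10 + 10 without a balancing factor, together with an analysis that names no baseline covariate, leaves the medication contrast (especially its opioid part) and, less strongly, the pain contrast open to chance imbalance.

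The correctable risk that two or more opioid users all fall in one arm is about 13% at 6% or 20% prevalence and 0.4% at 46%. An entry-pain gap of at least 0.5 SD occurs in about 26% of allocations. The first figures assume that the general cancer range applies to these children, and the second assumes roughly normal entry pain. Adjustment handles a partial imbalance. It cannot supply a contrast among opioid users if one arm has none, and in that case only description is honest. The change is worth making because its main part uses data that the trial already collects.

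**What to change.** **Section 3.18 (main change).** Analyse follow-up pain and medication dose adjusted for the baseline value of the same measure and for baseline opioid use (yes/no). Tabulate baseline opioid users by arm. Report the medication contrast as an estimate with an interval, and only descriptively if one arm has no baseline users. The cost is one or two degrees of freedom; no new data are needed, since Table 1 already schedules both measures at baseline.

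**Section 3.6 (optional, for allocations not yet made).** The staff member outside enrolment may prepare separate sealed envelope sets for baseline opioid users and non-users, in small blocks whose sizes vary at random and are not disclosed. The small blocks are essential. If the users' set were itself one long 10 + 10 list, the first three envelopes would still all name the same arm with probability 21%, as now. The cost is a second set of envelopes and a short amendment. The downsides are slightly more predictability and a final split that may be slightly off 10:10. No extra patients or visits are required.

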### Behavioral PA intervention

3.7

Participants who are randomized to the intervention group will participate in a 16-week behavioral PA intervention coupled with standard post-cancer directed treatment care. The intervention will be based on the Children's Oncology Group Guidelines for Diet and PA recommendations [35], the International Pediatric Oncology Exercise Guidelines [36], and on successful PA interventions ongoing at Penn State Children's Hospital.

The behavioral PA intervention will be structured to increase patients' PA behavior and to favor low intensity bodily movement (e.g., activities expending >1.5 to 3 metabolic equivalent (METS) or intensity <5 on a scale of 0–10), starting with a session duration of <15-min, three days per week. The session duration and frequency will increase over time. Participants will receive a set of resistance bands and a Fitbit (Inspire 3) at the beginning of the intervention, and they will be asked to wear their Fitbit every day (day and night) for the duration of the study. To note, data generated from the Fitbits will not be collected since the purpose of giving a Fitbit to participants is only for them to keep track of their physical activities.

The behavioral PA intervention will also include support calls and text messages from the research staff, as follows: weekly support calls (weeks 1–4), biweekly support calls (weeks 6 and 8) and texts (weeks 5 and 7), monthly support calls (weeks 12 and 16) and texts (weeks 9, 10, 11, 13, 14, 15). The behavioral PA intervention will be individualized according to patients' health status, results from the physical function assessment, and the most recent week's achieved PA. The intervention will be modified and adapted during weekly support calls or text messages, including frequency, intensity, time and type to maximize participants' success. The behavioral PA intervention will be conducted by an exercise physiologist and an exercise expert with specialty training in pediatric oncology.

